### Sample size calculation

Based on the literature and findings from a small pilot study that used metabolomic techniques, the sensitivity and specificity required to classify the control and PCOS groups will be 100% and 86%, respectively. The corresponding values between the control group and subgroup 1 will be 96.7% and 100%, respectively, while those between the control group and subgroup 2 will be 100% and 86.2%, respectively. The sensitivity and specificity for dividing PCOS into two different subtypes will be 90.9% and 87.5%, respectively. To meet the lower statistical limit, each subgroup will include at least 30 participants.

According to a presumptive maximum dropout tolerance of 20%, with a significance level of 0.05 and a power of 0.80, we calculate the required sample size for the experimental groups to be 216. In this trial, 60 people will be assigned to the healthy control group and 108 people to each experimental group across the three centers.

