## Methods

### Study design

This is a prospective, multicenter, analyst-blinded, randomized controlled trial. Subjects will be grouped into one healthy control group and two parallel experiment arms, as follows: (1) people without PCOS (healthy control group), (2) patients diagnosed with PCOS based on clinical indices (experimental group 1), and (3) patients diagnosed with PCOS based on metabolomic indices (experimental group 2). A total of 276 participants, including 60 people without PCOS and 216 patients with PCOS, will be recruited. The 216 patients with PCOS will be randomly assigned to the two experimental (diagnosis) groups in a 1:1 ratio. After group assignment, medical detection results, relative information, and biological samples will be collected from all three groups. Additionally, the blood samples from all participants will be tested using metabolomic methods for further study, while the analysis results will be totally blinded to all participants and their research physicians. Based on our previous study [3], we will categorize patients with PCOS into two subgroups: patients with hormone metabolism disorders (subgroup 1) and patients with lipid metabolism disorders (subgroup 2).

The two diagnosis groups will be automatically divided into the two different subgroups according to patient characteristics. The main difference is that in group 1, diagnosis will be based on clinical indices [1], such as clinical signs and symptoms and ultrasonography findings, while in group 2, diagnosis will be based on metabolomic indicators. All patients will receive treatment according to their subtype group, and the treatment will consist of Diane-35 or metformin. The intervention period for all experimental groups will be 6 months, and the results will be evaluated after the completion of three constant treatment sessions (3 months).

Outcomes will be assessed, and the data will be analyzed by someone blinded to the assignment of participants. The study design is shown in Fig. 1, and the timeline is presented in Figs. 2 and 3.

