### Outcome measurements

The healthy control group will remain enrolled in the trial until all their samples are collected. For the experimental groups, the primary outcome will be the changes in their relative PCOS condition evaluated using clinical indices. The main clinical index that will be evaluated is the LH/FSH ratio.

Secondary outcomes will be assessed using other indices, signs, and symptoms, as described in the 2018 Chinese Endocrine Society clinical practice consensus on PCOS [1] such as sex hormone-related indices (FSH, LH, prolactin, estradiol, progesterone, testosterone, anti-Müllerian hormone (AMH), and vitamin D), blood lipid-related indicators (total cholesterol, triglycerides, HDL, LDL, Apo A1, Apo B, lipoprotein(a), free fatty acids, and high-sensitivity C-reactive protein), and endocrine-related indicators (glucose and insulin (at 0, 30, and 120 min) and blood uric acid). To help evaluate the outcomes, three metabolic markers will also be used, namely, palmitoyl sphingomyelin, cyclic guanosine monophosphate, and DHEAS. Ultrasound results will also be evaluated, and the number and diameter of follicles in both ovaries will be measured.

Safety outcomes will include any severe impairment in liver function or inability of the patient to tolerate symptoms (e.g., nausea and vomiting caused by metformin) related to the therapeutic drugs. Such outcomes will be monitored after each treatment session (1 month) using the hepatic function test. An exploratory outcome will be complete recovery from PCOS after treatment within 26 weeks.

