### Statistical analyses

The dataset will include a safety set, a full analysis set (FAS), and a per-protocol set. The safety set is designed for participants who will be randomly assigned to receive at least one session of treatment. The FAS will include all medical data related to the trial and will indicate the intervention conducted; however, participants who miss the primary outcome evaluation will be excluded. In the per-protocol set, participants will be included if they receive at least three constant sessions of treatment.

In this trial, the FAS will be used for the basic analysis. For missing data, we will employ the imputation adjustment approach, and the last observation analysis will be selectively used to handle the missing data.

A sensitivity analysis will then be used to compare the results of the per-protocol analysis and the different intervention analyses to evaluate the impact of the missing data on the trial results.

Descriptive statistics about quantitative indicators, such as means, standard deviations, medians, minimums, and maximums, will be presented. Variance analysis will be used to compare the quantitative indices among the different groups (healthy control group and experimental groups 1 and 2), and the Student-Newman-Keuls test will be used to analyze the two subgroups.

Classification indicators will be described by the number and percentage of each category. The chi-squared test or exact probability method will be used to compare the qualitative indices among the three groups, and the chi-squared segmentation method will be used to compare the two pairwise subgroups.

SPSS version 21.0 will be used to analyze all trial data. All statistical tests will be double-sided, and statistical significance will be considered when the *p* value is ≤ 0.05.

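### The stated 80% power has no LH/FSH basis, and because both arms draw on the same two drugs it is implausible for the whole-arm comparison unless the two subtyping methods often disagree

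*Protocol article*

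**What the plan says.** Under Study design, the patients with PCOS "will be randomly assigned to the two experimental (diagnosis) groups in a 1:1 ratio". Group 1 is subtyped on clinical indices and group 2 on metabolomic indices. Then: "All patients will receive treatment according to their subtype group, and the treatment will consist of Diane-35 or metformin". The Metabolomic index group section names the method of subtyping as the main difference between the arms.

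Under Outcome measurements, the primary outcome is change in PCOS condition on clinical indices: "The main clinical index that will be evaluated is the LH/FSH ratio". Under Statistical analyses, quantitative indices are compared between whole groups by analysis of variance, and "All statistical tests will be double-sided".

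The Sample size calculation gives four pairs of accuracies. Three concern healthy controls against all PCOS or against one subtype; the first reads "the sensitivity and specificity required to classify the control and PCOS groups will be 100% and 86%, respectively". The fourth concerns subtype against subtype: "The sensitivity and specificity for dividing PCOS into two different subtypes will be 90.9% and 87.5%, respectively". It adds a minimum of 30 per subgroup and a "presumptive maximum dropout tolerance of 20" per cent, then concludes "with a significance level of 0.05 and a power of 0.80, we calculate the required sample size for the experimental groups to be 216".

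**The concern.** There are two linked problems.

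First, the power statement and the primary comparison concern different quantities. The randomised question is whether change in LH/FSH differs between groups 1 and 2. The printed inputs describe how well metabolomics separates controls from patients, or one subtype from the other. Nothing in the section is a difference between the randomised arms on LH/FSH.

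Second, the design dilutes whatever effect exists. A patient placed in the same subtype by both methods is assigned the same drug in either arm. Such patients add variance to the whole-arm comparison but little or no contrast. The section makes no allowance for this.

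A reader who trusts the 0.80 would take a null whole-arm result as evidence that metabolomic subtyping does not help. At low to moderate disagreement between the methods, the comparison would have had little chance of showing that it does.

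**Working it through.** **Inputs.** From the article: two-sided 0.05, power 0.80, 108 per arm, 20% dropout, and accuracies of 100/86%, 96.7/100%, 100/86.2% and 90.9/87.5%. Not in the article, so assumed over a range: the discordance rate q (share of patients whom the two methods subtype differently) and the mean effect δ among those patients, in SD of LH/FSH change.

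**Step 1: can 216 be reproduced?** Two-proportion formula, unpooled: n = (1.960 + 0.842)² × [p₁(1−p₁) + p₂(1−p₂)] / (p₁−p₂)², then divided by 0.8 for dropout. The target is 108 per arm.

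- Subtype pair, 90.9% v 87.5%: about 1,304 per arm before dropout.
- 96.7% v 86.2%: 107.4 per arm before dropout, 134 after. With pooled variance, 110 before and 138 after.
- 96.7% v 86.0%, pooled: 107.2 before dropout, 134 after.
- 96.7% v 86.2%, one-sided and pooled: 86.6 before dropout, 86.6/0.8 = 108.3 after. This matches numerically, but it sets a sensitivity against a specificity and contradicts the two-sided rule.
- Four subgroups of 30: 120/0.8 = 150 in total.
- A precision formula for 87.5% with a half-width of 7 points also gives 108 after dropout, but the article states no such width and a precision formula uses no power.

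No two-sided contrast of the stated accuracies that makes sense as a comparison of the arms gives 216.

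**Step 2: what 216 delivers for a comparison of means.** Evaluable per arm: 108 × 0.8 = 86.4, so 86. The normal approximation gives a detectable difference of √(2/86) × (1.960 + 0.842) = 0.427 SD; the t-test gives 0.430 SD. The article states no such effect.

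**Step 3: dilution.** If concordant patients are treated alike, the whole-arm difference is about Δ = q × δ. The effect needed among discordant patients for 80% power is therefore 0.430/q. Power below is for a two-sided t-test with 86 per arm.

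| Assumed q | δ needed for 80% power | Whole-arm power if δ = 0.8 SD | Whole-arm power if δ = 1.0 SD |
|---|---|---|---|
| 10% | 4.3 SD | 8% | 10% |
| 20% | 2.1 SD | 18% | 26% |
| 30% | 1.4 SD | 35% | 50% |
| 50% | 0.86 SD | 74% | 90% |

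**Step 4: direction.** Discordance runs two ways, with the drugs swapped between arms, so qδ is really q₁δ₁ + q₂δ₂. If one drug simply moves LH/FSH more than the other whatever the subtype, δ₁ and δ₂ have opposite signs and partly cancel. The table ignores this. Where such cancellation occurs, a given size of effect within each direction yields less power than the table shows.

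**The case against.** An article condenses its protocol, and a fuller document may hold an LH/FSH effect size. Accuracy is also a stated aim of the trial, so accuracy figures are not out of place. Both points are fair, but the article prints its inputs directly before its power claim, and those inputs neither concern the primary comparison nor yield the number.

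Four stronger readings are tempting, and the document does not support them.

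- *Discordance is about 11%.* With an even subtype mix, 0.5 × 9.1% + 0.5 × 12.5% = 10.8%. This requires 90.9% and 87.5% to measure agreement with the clinical subtype, and no reference standard is given. The Background says the two subgroups were found by mass spectrometry, so the reference may itself be metabolomic. The good correlation reported in the Discussion concerns individual markers. Against it, the Background warns of misdiagnosis under heterogeneous criteria, the Discussion says precise diagnosis is very difficult, and Study limitations calls consistent group 1 diagnosis the main difficulty. Discordance could be large.
- *Only discordant patients can differ between arms.* Under Blinding, group 1 treatment follows clinical practice, whereas group 2 physicians may not change the scheme. Some difference in concordant patients is possible, hence mainly rather than only.
- *216 was computed from the accuracies.* The article does not say so. They are simply the only effect-type inputs it shows.
- *The primary analysis should be confined to discordant patients.* The whole-arm contrast is a legitimate comparison of two diagnostic strategies, and replacing it is a choice of estimand. Group 1 is treated on the treating physician's subtype, which a later re-classification may not match, and pooling both swap directions may cancel effects.

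**Conclusion.** The point holds in this form: 0.80 is unsupported as the power of the group 1 versus group 2 comparison on LH/FSH, and it is implausible at low to moderate discordance. The 0.43 SD figure rests only on the article's 108 per arm, 20% dropout and two-sided 0.05. The figures for discordant patients also need an assumed q and approximately equal treatment of concordant patients. The true power cannot be calculated, because the discordance rate, the effect and the SD are not given. It could reach 80% with, for example, 50% discordance and an effect of 0.86 SD, so the article does not support saying that the trial certainly falls short.

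**What to change.** 1. Replace the power sentence. State that 216 randomised leaves about 86 evaluable per arm, which gives 80% power (two-sided 0.05) for a whole-arm difference of about 0.43 SD in LH/FSH change. Add that this is equivalent to about 4.3, 2.1, 1.4 and 0.86 SD among discordant patients at an assumed 10%, 20%, 30% and 50% discordance.
2. State that a null whole-arm result does not by itself show that metabolomic subtyping is unhelpful.
3. Keep the whole-arm comparison primary. Fix before unblinding a supportive comparison of group 1 with group 2 in discordant patients, reported by direction of discordance. Use the metabolomic subtype, which Study design has measured in everyone, and a baseline clinical subtype assigned in the same way in both arms, blind to arm and to metabolomics. Both are baseline classifications, so randomisation protects the comparison.

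**Cost.** The first two items are wording; recruitment is reported as complete, so the sample size itself is no longer open. The third needs a baseline chart classification of all 216 patients, for which the three-physician diagnosis team described under Study limitations could serve. The stated power becomes less favourable. The supportive analysis is small if discordance is low: at 10%, about 86 × 0.10 = 8.6 patients per arm, before splitting by direction. It is also diluted wherever its clinical subtype differs from the one that set treatment in group 1.

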### Quality control

During the trial, quality control will be carried out by the steering committee. All researchers are required to attend training on trial methods, techniques, and protocol regulations to maintain data consistency and validity. Any modifications or corrections required will be discussed, decided upon, and submitted to the steering and ethics committees. Patient details will be kept confidential throughout the trial.

## Discussion

PCOS is a syndrome characterized by various signs and symptoms, such as androgen excess, ovarian dysfunction, and a polycystic ovarian morphology. Considering its high prevalence among reproductive women in China and given that its complications may lead to endometriosis, endometrial cancer, or some malignant diseases, PCOS might be one of the most common and severe endocrine and metabolic disorders.

The diagnosis of PCOS still depends on ruling out other diseases [24–29] including thyroid dysfunction, nonclassical congenital adrenal hyperplasia, and androgen-secreting tumors. PCOS has several recognized phenotypes that present with distinct characteristics and require individualized treatment [1]. However, with the lack of classification criteria, it is very difficult for physicians to make a precise diagnosis and develop a suitable treatment strategy.

Of note, researchers have attempted to determine whether there are biomarkers that could be used as predictive markers for the different PCOS phenotypes. Zhang et al. [30] found that the phenotype with hyperandrogenism is associated with a higher score in the homeostatic model assessment of insulin resistance (HOMA-IR) than the other phenotypes (without androgen excess). Further detection showed that serum irisin levels are associated with hyperandrogenism but not with oligo-anovulation or PCOS morphology. Additionally, Minooee et al. [31] pointed out that the testosterone-to-androstenedione ratio is associated with insulin resistance (sensitivity 0.83, specificity 0.42) and MetS (sensitivity 0.85, specificity 0.70) among patients with PCOS, indicating the strong link between insulin resistance and hyperandrogenism. This finding may assist clinicians and researchers in classifying the specific phenotypes of PCOS. However, Bozic-Antic et al. [32] designed a cross-sectional clinical study of 365 women with PCOS and 125 healthy controls from a Caucasian population. In their study, patients with PCOS were divided into groups based on four phenotypes, according to the criteria of the European Society of Human Reproduction and Embryology (ESHRE)/American Society for Reproductive Medicine (ASRM) [33]. Their findings suggested that all phenotypes are associated with the same prevalence of MetS, but phenotype B was associated with a different cardiovascular risk. This difference might partly be related to epigenetic and environmental influences. Moreover, the free androgen index [34], serum AMH level [35–38], PPARGC1A (a leukocyte methylation promoter) [39], and some other indices were also found to be potential biomarkers for predicting PCOS and classifying its phenotypes. Although there have been many efforts to address the predicament surrounding the diagnosis of PCOS, the precise classification criteria have yet to be developed. However, there has been a turning point in the detection methodology with the advent of metabolomics.

This trial is designed to explore a more specific and sensitive method to determine the subtypes of PCOS. Based on the preliminary study, our team found that clinical indicators such as the LH/FSH ratio and Apo A1, AMH, and insulin levels had a good correlation with metabolomic results. This finding indicates the potential of developing a diagnostic and therapeutic strategy for PCOS based on an integrated biomarker system.

To further investigate the findings of this trial, we will conduct a prospective cohort study, expanding the sample size of patients with PCOS and analyzing the detection frequencies. This study is a multicenter, randomized, open-label, blinded clinical study aiming to standardize the diagnostic classification and treatment of PCOS. The sensitivity and specificity of integrating metabolomic indices in the diagnostic criteria will be compared with diagnosing the disease with clinical indices alone. Our findings may help improve the empirical classification, find predictive biomarkers, and assist in establishing an integrated biomarker system for developing precise diagnostic and treatment strategies for different PCOS subgroups in the future.

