**Discussion:**

The results of this trial should help to determine whether using metabolomic indices is more accurate and effective than using clinical characteristics in diagnosing the phenotypes of PCOS. The results could provide a solid foundation for the accurate diagnosis of different PCOS subgroups and for future research on individualized PCOS therapy.

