This trial aims to compare the accuracy and efficacy between using metabolomic indices and using clinical characteristics in diagnosing PCOS phenotypes. Our findings could provide a basis for further research on individualized PCOS therapy.

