### Inclusion criteria

Participants who meet all of the following criteria will be enrolled in the experimental groups:
Diagnosed with PCOS according to the 2018 Chinese Endocrine Society clinical practice consensus, i.e., presence of at least two of the following three conditions, excluding other etiologies: (a) clinical or biochemical hyperandrogenism, (b) oligo-anovulation (menstrual cycle length of > 35 days and having eight or fewer menstrual cycles per year), and (c) a polycystic ovarian morphology characterized by at least 25 small follicles (2–9 mm) in the entire ovary and/or an increase in ovarian volume of ≥ 10 mLA reproductive woman aged 18–45 yearsAble and willing to comply with the interventions and follow-up evaluations

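### The planned conclusion that metabolomic indices are more accurate than clinical ones has no usable reference: PCOS status is set by the clinical criteria, and subtype has only the two competing labels

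*Protocol article*

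**What the plan says.** The end of the Background gives the aim: "This trial aims to compare the accuracy and efficacy between using metabolomic indices and using clinical characteristics in diagnosing PCOS phenotypes". The Discussion part of the Abstract says the results should help to "determine whether using metabolomic indices is more accurate and effective than using clinical characteristics in diagnosing the phenotypes of PCOS". Follow-up again lists accuracy of diagnosis among the things to be evaluated, and Data collection and monitoring has an assessment of diagnostic accuracy entered in the case report forms. The main Discussion names the measures: "The sensitivity and specificity of integrating metabolomic indices in the diagnostic criteria will be compared with diagnosing the disease with clinical indices alone".

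The entry rule for patients is "Diagnosed with PCOS according to the 2018 Chinese Endocrine Society clinical practice consensus, i.e., presence of at least two of the following three conditions". Participants and recruitment cites reference [1] for that consensus. Study design cites the same reference for the comparator: "in group 1, diagnosis will be based on clinical indices [1], such as clinical signs and symptoms and ultrasonography findings". Controls enter only if they do not have PCOS (Interventions, Healthy control group).

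Subtype (hormone or lipid metabolism disorder) is assigned clinically in group 1 and from metabolomic indices in group 2. The primary outcome is change in clinical indices, mainly the LH/FSH ratio (Outcome measurements).

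**The concern.** Sensitivity and specificity need a reference that is separate from the methods being judged. The article names none, and what it does fix points to two different problems.

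- **PCOS versus no PCOS.** The available truth is entry status, which is itself the clinical diagnosis.
- **Hormone versus lipid subtype.** The entry criteria do not define the subtypes, so the only labels are those produced by the two methods.

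At stake is the accuracy half of the aim. A published statement that one method is more accurate would reflect the choice of reference, not the performance of the methods. Group 2 is also described, in the Abstract and in Study design, as patients whose PCOS is diagnosed by metabolomics. In fact these patients enter by the clinical criteria and only their subtype is set by metabolomics. The label invites the reader to see a diagnostic comparison that is not made.

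**Working it through.** **Inputs.** 216 patients and 60 controls (Study design). Metabolomic sensitivity 100% and specificity 86% for control versus PCOS, and 90.9% and 87.5% for the two subtypes (Sample size calculation). That section gives no accuracy figure for the clinical method and names no reference. It also states no effect size behind the 216, so there is no plan figure to reproduce here. Nothing below depends on the derivation of 216.

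**Step 1: PCOS versus no PCOS, scored against entry status.** This assumes that freedom from PCOS in controls is judged clinically. The article mentions a medical evaluation at entry and collects study blood only afterwards.

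- Clinical sensitivity = 216/216 = 100%.
- Clinical specificity = 60/60 = 100%.
- Metabolomic errors among controls at 86% specificity = 60 × (1 − 0.86) = 8.4, so about 52 of 60 correct.
- Apparent difference in specificity = 100 − 86 = 14 points.

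No rule, metabolomic or combined, can score above a method that is itself the reference.

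**Step 2: subtype, with the clinical label as reference.** Suppose metabolomics were perfect and the clinical label had sensitivity and specificity both equal to c, with a share π of patients truly in subtype 1. The values of c and π are assumptions.

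- Apparent sensitivity = πc / [πc + (1 − π)(1 − c)].
- Apparent specificity = (1 − π)c / [(1 − π)c + π(1 − c)].

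| π | c | Apparent sensitivity | Apparent specificity |
|---|---|---|---|
| 0.5 | 0.70 | 70% | 70% |
| 0.5 | 0.80 | 80% | 80% |
| 0.5 | 0.90 | 90% | 90% |
| 0.3 | 0.70 | 50% | 84.5% |
| 0.7 | 0.90 | 95.5% | 79.4% |

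So a perfect test appears imperfect, by an amount that depends on the unknown error of the reference. With the metabolomic label as reference, metabolomics scores 100% on both measures by construction. The ranking follows the choice of reference.

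**Step 3: is there another reference in the text?** The three-physician team in Study limitations is clinical, and it sees only cases whose subtype the treating physicians cannot settle. It is neither independent of the clinical method nor applied to everyone. The main Discussion itself says that agreed classification criteria are lacking. The LH/FSH outcome can compare the two strategies, but it is not a sensitivity or a specificity.

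**Step 4: what agreement could show.** Take 89% agreement as an illustration; it is not a document figure.

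- Group 1 (108 patients): half-width of the 95% CI = 1.96 × √(0.89 × 0.11/108) = 5.9 points; discordant patients = 108 × 0.11 ≈ 12.
- All 216: half-width = 1.96 × √(0.89 × 0.11/216) = 4.2 points; discordant patients = 216 × 0.11 ≈ 24, or about 12 per arm before the 20% dropout allowed for.

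**The case against.** **The Discussion sentence may not be about this trial.** It follows a sentence on a later cohort study, and its paragraph speaks of an open-label study, which does not fit the blinding described elsewhere. That ambiguity is real. The study it describes is, however, multicenter and randomized, which fits this trial. The accuracy promise also stands without it, in the Abstract, Background, Follow-up and Data collection sections, although those do not name sensitivity and specificity.

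**The aim concerns phenotypes, which the entry criteria do not define.** This stands. The circularity and the 8-of-60 figure apply only to PCOS versus control. A reader might infer that the whole comparison is decided before any data are seen. The documents do not support that: for subtypes the result is undefined, not predetermined, and no section says that entry status will be the reference.

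**Without a gold standard, randomised outcomes are a recognised way to judge a classification.** This also stands. A reader might infer that the trial can say nothing about the two methods. That is not so: the comparison of treatment outcome between the two subtyping strategies remains valid. It answers a question of effect, not of accuracy.

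**The full protocol or analysis plan may define a reference.** It could for subtype. It could not undo the circularity at disease level while entry and comparator rest on the same clinical consensus.

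**Conclusion.** The point holds in this limited form: the design does not support a conclusion that one method is more accurate.

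- At disease level, scoring against entry status gives clinical diagnosis 100% on both measures. Metabolomics would appear 14 points less specific at the protocol's own figure, about 8 of 60 controls against 0. That gap says nothing about which method is truly better.
- At subtype level no size can be given, because neither label is a reference.

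This rests on three readings: that the Discussion paragraph describes this trial, that controls are cleared of PCOS clinically, and that the 86% applies to controls. If the first reading fails, the accuracy aim in the Background and Abstract still lacks a reference. It should be corrected before results are reported; it does not threaten the randomised treatment comparison.

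**What to change.** 1. Remove the claims that the two methods' sensitivity and specificity will be compared and that one will be shown more accurate.
2. Restate the aim and planned conclusion as the effect of metabolomic versus clinical subtyping on treatment outcome.
3. Report metabolomic sensitivity and specificity against controls only as performance against clinical diagnosis.
4. Describe group 2 as subtyped, not diagnosed, by metabolomics.
5. Report percent agreement and kappa, each with a 95% CI, between clinical and metabolomic subtype in group 1, where the clinical label is assigned and all blood is tested by metabolomics. Extend this to group 2 only if a clinical subtype can be assigned from baseline data blind to the metabolomic allocation.
6. Treat outcomes in discordant patients as exploratory only, given the small numbers in Step 4.

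Items 1 to 4 cost only wording, and item 5 in group 1 uses data already planned. Extending it to group 2 costs more: the treating physicians there are told the subgroup, so separate blinded raters would be needed. The downside is a less ambitious claim about accuracy.
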